**Table 4 – Outcomes and examples of potential scales to measure mediators and moderators**

| Domain                          | Name of Variable                    | Variable Description                                                      | Potential Time Points Administered  | Measure               |
|----------------------------------------|--------------------------------------------|----------------------------------------------------------------------------------|--------------------------------------------|------------------------------|
| Outcomes – Effectiveness        | Number of unprotected sex acts in x period | # episodes of unprotected intercourse (vaginal/anal) in the last week/month only | Baseline and 2, 4, 8, 12, 16, 20, 24 weeks |                              |
| Potential Mediators/ Moderators | Motivation to avoid unsafe sex             | 9-item scale: HIV risk-avoidance intention                                       | Baseline and 2, 4, 8, 12, 16, 20, 24 weeks | Kalichman, 96                |
|                                        | Self-efficacy                              | 6 items, 4 point response set                                                    | Baseline and 2, 4, 8, 12, 16, 20, 24 weeks | Kalichman, 06                |
|                                        | Perceived infectiousness                   | Perceptions of infectiousness related to stage of infection                      | Baseline and 2, 4, 8, 12, 16, 20, 24 weeks | Adapted from Kalichman, 2002 |
|                                        | Ambivalence                                | 16-item, 4-point scale on ambivalence related to safer sex behavior              | Baseline and 4, 8, 12, 16, 24 weeks        | Thompson, 1995               |
|                                        | Substance use                              | Drug/alcohol use and frequency                                                   | Baseline and 4, 8, 12, 16, 24 weeks        |                              |
|                                        | Social support                             | 15-item, 4-point scale of available support                                      | Baseline and 8, 24 weeks                   | Kalichman, 99                |

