#### 7.6.2 Secondary Analysis

Standard descriptive statistics, such as means, medians, variance, and interquartile ranges for continuous variables and proportions for binary variables will be used to summarize the characteristics of sexual behavior, depression, substance use, and motivation for safe sex at baseline and/or subsequent study visits in both study arms. For categorical variables, the numbers and the proportions will be tabulated. **Particularly, for each participant, the pre-post difference at each visit and the difference between current and previous visits will be visually explored to look for any trend using a single-case analysis approach. A case study and mixed-methods (e.g. using both qualitative and quantitative data) approach will also be considered in the single-case situation to better understand the intervention effect among particular study subjects. Some nonparametric smoothing will be considered to fit the longitudinal curves to further explore the trends.**

To assess the efficacy of the intervention on sexual behaviors, such as self-reported unprotected sex acts with the intervention, Poisson regression will be used for count endpoints based on generalized estimation equations (Liang, Zeger, et al., 1986). Effects of the intervention on sexual behaviors at each time point will be assessed to see whether there are differences in behaviors after the intervention or at any time. In addition, to determine whether there are changes in behavior after viral loads have stabilized, behaviors will be compared before and after 12 weeks post-diagnosis. A robust variance estimator will be used to correct for correlation among the longitudinal measures at baseline and post-intervention follow-up visits. If over-dispersion exists, quasi-Poisson or negative binomial model will be used. A Wald test will be used to test whether the intervention has significant effect on reducing sexual risk behaviors compared to the control arm. It will be a two-sided test at a significance level of 0.05. **Given all the participants are acute or early HIV-infected, it is possible that there may be few, if any, unprotected sex acts reported. Therefore, the negative binomial assumption might not hold and a non-parametric approach will be considered. Specifically, unprotected sex acts will be categorized into 2 or 3 groups. At each visit, a Fisher exact test will be used to test proportions difference for two arms and exact p-values will be calculated.**

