The impact of mediator variables (Table 4) on mediating the effects of the intervention on self-reported unprotected sex behaviors will be assessed. Multivariate analysis of variance (MANOVA) will be used to determine the relationship between intervention and changes in the mediator variables with repeated measures over the visits if the normality assumption holds. For the categorical variables, Chi-squared tests will be used to test independence between intervention and mediator variables at each visit.

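### Section 7.6.2 promises a mediation assessment, but the methods it names test only whether arm changes the mediator; the MANOVA also depends on complete attendance

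*Protocol*

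**What the plan says.** Section 7.6.2 of the Protocol sets the aim: "The impact of mediator variables (Table 4) on mediating the effects of the intervention on self-reported unprotected sex behaviors will be assessed". Two methods follow.

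- Continuous mediators: "Multivariate analysis of variance (MANOVA) will be used to determine the relationship between intervention and changes in the mediator variables with repeated measures", to be applied "if the normality assumption holds". No alternative is named if normality fails.
- Categorical mediators: "Chi-squared tests will be used to test independence between intervention and mediator variables at each visit".

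The behavior outcome has its own model in the same section: "Poisson regression will be used for count endpoints based on generalized estimation equations", with a Wald test of the arm effect. No mediator term is named in it.

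Table 4 lists nine potential mediators or moderators. Motivation, self-efficacy and perceived infectiousness are scheduled at "Baseline and 2, 4, 8, 12, 16, 20, 24 weeks". Ambivalence and substance use have 5 follow-ups. Social support, depression, coping and sexual coercion have 2, at weeks 8 and 24. The column is headed as potential time points, and section 7.2.2 calls the entries examples and concedes that numbers will be small.

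**The concern.** Mediation needs two links: arm changes the mediator, and the mediator, given arm, is related to behavior. The named methods cover only the first. A significant MANOVA or chi-squared result is fully compatible with no mediated effect, so a reader who took such a result as evidence on mechanism would be misled.

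The choice of MANOVA adds a practical problem. In its classical form it needs every scheduled measurement on a participant, so one missed assessment of a mediator removes that person from that mediator's analysis. The estimate would then rest on the best attenders of an already small trial.

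Perceived infectiousness raises the stakes slightly. It is a secondary endpoint (section 7.2.2), and section 2.3 says perceptions will be compared between arms. The efficacy model in section 7.6.2 is written for sexual behaviors, so the mediator paragraph holds the only named between-arm test for this endpoint.

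**Working it through.** **1. Does any named method answer the stated question?**

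| Analysis in 7.6.2 | Response | Explanatory variable | Link tested |
|---|---|---|---|
| Repeated-measures MANOVA | mediator change | arm | arm to mediator |
| Per-visit chi-squared | mediator category | arm | arm to mediator |
| Poisson GEE | unprotected acts | arm | arm to behavior |

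No row has behavior as response and a mediator as explanatory variable, and no indirect effect is named.

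**2. Complete cases under MANOVA**

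The Protocol gives no figure for the mediator analysis, so there is none to reproduce. Its nearest design figures, 92% and 62% power for unprotected acts (section 7.3), came out at 93.1% and 61.8% by simulation with a t-test and are not in dispute.

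Inputs: 46 participants, about 23 per arm (section 7.3), and 7, 5 or 2 follow-ups (Table 4). The per-visit attendance *q* is an assumption, because the Protocol states none. Baseline is taken as complete and absences as independent across visits.

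Formula: complete cases = 46 × q^k, with *k* follow-ups.

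| q | k = 7 (3 mediators) | k = 5 (2 mediators) | k = 2 (4 mediators) | any single visit (46 × q) |
|---|---|---|---|---|
| 0.95 | 46 × 0.698 = 32.1 | 46 × 0.774 = 35.6 | 46 × 0.9025 = 41.5 | 43.7 |
| 0.90 | 46 × 0.478 = 22.0 | 46 × 0.590 = 27.2 | 46 × 0.81 = 37.3 | 41.4 |
| 0.85 | 46 × 0.321 = 14.7 | 46 × 0.444 = 20.4 | 46 × 0.7225 = 33.2 | 39.1 |

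Independence makes the loss large. If the same people missed every visit, the last column would apply to MANOVA too. At 90% attendance the 7-follow-up mediators would therefore keep between 22 (independent) and 41 (fully clustered).

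As an illustration only, a multivariate two-sample test on 7 follow-up scores was simulated with an assumed shift of 0.8 SD at every visit and within-person correlation 0.5. Power was about 65% with no absences, and 43%, 26% and 12% at 5%, 10% and 15% missed per visit.

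**3. Chi-squared at each visit**

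Each test loses only those absent at that visit (last column). The issue is consistency. Sections 7.3 and 7.6.1.1 choose exact intervals because the sample is not large. Section 7.6.1.1 compares two proportions by Fisher's test, and section 7.6.2 uses Fisher's test per visit for grouped sex acts. With 23 per arm, a category with pooled proportion *p* has expected count 23*p*. This is below the usual rule-of-thumb value of 5 when p < 5/23 = 0.22. Balanced binary mediators (23 × 0.5 = 11.5) are unaffected; uncommon categories are not.

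**The case against.** Several stronger readings are tempting and are not supported.

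- A reader might infer that both methods discard anyone with a missed visit. That is wrong for the chi-squared tests, which are run visit by visit.
- A reader might take the loss to 22 of 46 as typical. It applies to 3 of 9 listed mediators, on a schedule labelled potential, at an assumed attendance and with independent absences. Tracing through CHAVI 001 (section 3.4), off-site assessments (section 5.0) and windows of 2 weeks either side from week 12 (section 5.3) all favor attendance.
- A reader might conclude that the Protocol orders deletion of incomplete cases. It does not. Complete-case use is a property of classical MANOVA, and the statistical analysis plan, which is not at hand, may deal with missing data.
- A reader might say that mediation cannot be assessed at all. The text does not rule out a further model; it simply names none.

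It is also fair that mediation is neither an objective nor an endpoint, that section 7.3 disclaims power for efficacy, and that an indirect effect in 46 people would be imprecise under any method. Perceptions are also explored in interviews (section 2.3).

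These arguments limit the consequence. They do not close the gap: neither better attendance nor a missing-data rule turns an arm-to-mediator test into a mediation analysis.

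**Conclusion.** The mismatch stands. Section 7.6.2 states a mediation question and fixes methods that address only its first half. This needs no assumption, because it can be read from the one paragraph together with the outcome model before it.

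The complete-case point stands for MANOVA alone. Its size depends on assumed, independent attendance. Over 95% to 85% per visit, about 32 down to 15 of 46 remain for the mediators with 7 follow-ups, and about 41 down to 33 for those with 2. Clustered absences would lose fewer.

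The chi-squared point is a small inconsistency with the Protocol's own use of Fisher's test. Overall severity is minor: the consequence is confined to the secondary mediator analyses and the only named between-arm test of perceived infectiousness.

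**What to change.** 1. Replace MANOVA with a linear mixed model on all available visits, with arm, visit, arm-by-visit, baseline score and site. Report arm contrasts that keep the periods before and after week 12 separate, since section 7.6.2 wants behavior compared across that point. Say what will be done if normality fails.
2. Use Fisher's exact test for categorical mediators at each visit, as is already done for grouped sex acts.
3. Settle the aim in one of two ways.
   - Reword it to intervention effects on potential mediators.
   - Or add a model, labelled exploratory, of unprotected acts (in Table 4's recall period) on arm and a mediator measured after randomization and before the outcome. Give a bootstrap interval for the indirect effect and a stated caveat on mediator-outcome confounding and imprecision. The baseline score is taken before randomization (section 5.1) and cannot serve as the mediator. The recall window must also begin after the mediator is measured: a one-month recall at week 4 reaches back before a week 2 score.

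The cost is wording and standard software, with no change to data collection. The mixed model assumes data are missing at random, which should be stated. Rewording the aim is the cheaper option.

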### **7.6.3 Qualitative Data Analysis**

Qualitative data will be collected on the acceptability of the intervention, intervention effectiveness, and sexual behavior and perception in order to help answer the primary and secondary objectives. The same analysis techniques will be applied to all qualitative data. Data analysis will begin with site staff transcribing and translating each audio taped interview. Sites may choose to simultaneously transcribe and translate the interview text from the original language to English or they may choose to transcribe the interview text in to the local language used during the interview and then translate it into English. A standardized transcription process will be followed.

As soon as possible after the interviews are conducted, transcript text will be read and re-read carefully by designated site staff and/or Protocol Co-chairs or their designees to: (1) become familiar with each individual situation; (2) identify text that may be unclear due to differences in the cultural context; (3) point out areas in which interviewing and transcription techniques could be improved; and (4) identify recurrent themes and areas for future probing.

Analysis will begin by creating codes for retrieving text from interview transcripts related to acceptability, intervention effectiveness, and sexual behavior and perception. Data-derived codes related to the overall objectives may also be used if identified through inductive coding and retrieving. The Protocol Chairs, site PIs, and study analysts will determine a coding frame to be used based on the qualitative questionnaires and the first few interviews available for analysis. NVIVO or another qualitative software program will be used to organize all qualitative data and prepare it for analysis. Procedures will be put into place to check for inter-coder reliability. Discrepancies will be noted, discussed, and resolved by the Protocol Co-chairs, site PIs, and study analysts. The resolution of such discrepancies will be amended to the existing coding

framework. Once all the transcripts have been coded, textual coding reports will be produced. Data display matrices will be developed to examine each code in detail for sub-themes and patterns across the interviews, followed by data summaries.

As in most studies where qualitative interviewing is used, questions may be modified, added to, or deleted from the qualitative questionnaires during data collection based on information that is learned from conducting and reading the transcripts from the previous interviews. We will also modify the questionnaire as appropriate after the training practice sessions. Grounded in qualitative methodology, this approach allows researchers to explore in more detail themes that emerge during data collection, and improves understanding of the overall issues. These modifications to the question guides will be made after approval from the ethics committees (EC)/institutional review boards (IRB) and will not be resubmitted; however, *only* probes and questions that are related to the overall topics described in this protocol and similar to the original questions will be added. Any changes made to the question guides that are beyond the topics described here will be resubmitted for EC/IRB review and approval prior to use. Limited changes will be made to questions that assess the acceptability of the intervention so comparable questions are asked to all participants.

## **8.0 HUMAN SUBJECTS CONSIDERATIONS**

### **8.1 Ethical Review**

This protocol and the informed-consent form template contained in Appendix II -- and any subsequent modifications -- will be reviewed and approved by the HPTN Scientific Review Committee and DAIDS Prevention Science Review Committee with respect to scientific content and compliance with applicable research and human subjects regulations.

The protocol, site-specific informed consent forms, participant education and recruitment materials, and other requested documents -- and any subsequent modifications -- also will be reviewed and approved by the ethical review bodies responsible for oversight of research conducted at the study site.

Subsequent to initial review and approval, the responsible IRBs/ECs will review the protocol at least annually. The Investigator will make progress reports to the IRBs/ECs at least annually, and within three months of study termination or completion. These reports will include the total number of participants enrolled in the study, the number of participants who completed the study, all changes in the research activity, and all unanticipated problems involving risks to human subjects or others. Study sites will submit documentation of continuing review to the DAIDS Protocol Registration Office in accordance with the current DAIDS Protocol Registration Policy and Procedure Manual which can be found on the following website: <http://rcc.tech-res.com/>

### **8.2 Informed Consent**

Written informed consent will be obtained from each study participant and also from counselors who deliver the intervention, using different consent forms from CHAVI 001. Each study site is responsible for developing study informed consent forms for local use (based on the templates in Appendix IIA and IIB) that describe the purpose of the study, the procedures to be followed, and the risks and benefits of participation, in accordance with all applicable regulations. The HPTN Coordinating and Operations Center (CORE) will work closely with the study site to ensure that the informed consent forms are translated into local languages, and that the accuracy of the translation is verified by performing an independent back-translation.

Literate participants will document their provision of informed consent by signing their informed consent form. Non-literate participants will be asked to document their informed consent by marking their informed consent form (e.g., with an X, thumbprint, or other mark) in the presence of a literate third-party, impartial witness. (Further details regarding DAIDS requirements for documenting the informed consent process with both literate and non-literate participants are provided in the *Requirements for Source Documentation in DAIDS Funded and/or Sponsored Clinical Trials*.) Any other local IRB/EC requirements for obtaining informed consent from non-literate persons also will be followed.

Participants will be provided with copies of their informed consent forms if they are willing to receive them.

It will be stressed with each potential participant with AHI that participation in this study is completely voluntary and is independent from her/his participation in CHAVI 001. Potential participants will be told that if they choose not to participate, there will be no penalty; they can continue to participate in other research studies, including CHAVI 001, or programs at the site and there will be no changes in the services they may receive at the clinic where they were contacted about this study.

Counselors who deliver the intervention will be asked to sign a separate consent form indicating that they agree to be interviewed approximately three times to capture their perceptions of the acceptability and perceived impact of the intervention.

### **8.3 Risks**

This is an intervention study involving extensive individual counseling. No biological specimens will be collected and there is no biomedical intervention. Participants may become embarrassed, worried, or anxious when completing their HIV risk assessment and/or discussing sexual behaviors and other issues related to the prevention of HIV, such as partner disclosure, during the intervention. The counselors who deliver the intervention are trained to help participants deal with these feelings. It will also be emphasized that participants may feel free not to answer a question asked during any assessment and to terminate any interview or leave the behavioral intervention sessions at any time.

Although study sites will make every effort to protect participant privacy and confidentiality, it is possible that participants' involvement in the study could become known to others and that social harms may result (i.e., because participants could become known as HIV-infected or at "high risk" for HIV infection or "high risk" for HIV transmission). For example, participants could be treated unfairly or discriminated against, or they could have problems being accepted by their families and/or communities. Finally, state or local officials may require study sites to report the names of study participants who disclose (in the context of a counseling session or in response to a questionnaire) an intention to harm self or others, current or recent child abuse, or current or recent statutory rape.

The risks will be described in the study consent form and will be thoroughly discussed with all potential study participants prior to participation.

CHAVI 011 data suggest that risks of violence from partner notification may be extremely limited; however, participants described the termination of relationships as a result of disclosure and many expressed fears of their partner's reactions and fears of discrimination from family/friends/community as a result of disclosure. These findings heavily informed the partner notification component of the HPTN 062 curricula. To reduce possible harm as a result of

partner notification, partner notification is an optional component of the experimental intervention. For participants who chose to disclose, they select the method which is most comfortable to them. If a participant chooses to notify partners, a full discussion of the potential risks will be discussed during the intervention session.

If requested by the participant, study staff may contact the partners of any participant reporting harm as a result of disclosure. For participants who wish for staff to notify their partner(s), only individuals who provide verbal consent for providers to contact partners will have partners contacted. Potential harm will be further minimized during a provider notification process by not disclosing the name or any personal information about the sex partner to those who are contacted by the study staff, unless the participant consents to providing this information. Staff will document in the participant's clinic notes that the participant gave permission to contact her/his sexual partner(s) and whether or not staff can disclose the participant's name to the partner(s). Additionally, when contacting the partner(s), study staff will first confirm the identity of the partner using the partner's name and other key identifying features provided by the study subject before providing any notification information. Study staff will also never leave study documents with a friend/family member to pass on to the partner.

Currently, there are no local or national requirements for disclosure of HIV status in Malawi. However, if local or national requirements are established during the course of the study then they will be followed.

There are no anticipated risks for counselors who participate in the assessments, as they are participating in this study in a professional role.

